#### Tanzania

A simple random sample of 30 ‘streets’ (neighbourhoods) will be selected from across the 15 urban and semiurban wards of Ilemela District. The boundaries of each selected street will be identified and mapped using Global Positioning System (GPS) devices,^19^ and within each street, we will randomly select 50 GPS coordinates using ArcGIS software V.9.3 (Esri, Redlands, USA).^20^ All households whose front doors are located within a radius of 20 m around the GPS point will be visited and all eligible consenting girls aged 15–19 years residing in these households invited to be interviewed. We aim to interview 166 girls per street. In order to reach our target sample size of 127 cohabiting adults, we estimated that for every 10 sexually active adolescent girls aged 15–19 years interviewed, one will be systematically selected and asked permission to interview her husband (married girls) or a cohabiting adult (unmarried girls).

### Data collection

The questionnaires will be adapted from various research instruments that have been used and validated in the study countries, including DHSs^7–9^ and FP2020 surveys.^1^ They will be developed in English and then translated into the local languages of the study communities. Final modifications will be made to the questionnaires following an extensive pretesting exercise and after pilot surveys are conducted in communities outside of the selected study sites.

Questionnaires will be administered face-to-face by female interviewers aged between 18 and 26 years. For households with potentially eligible study participants who are not at home, we will attempt to revisit up to twice (three visits in total). Data will be collected and recorded electronically in the field via tablets. This allows improved data quality through real time data delivery, built-in logical checks and skip patterns.

### Study outcomes

Our primary outcome, the mCPR among 15–19 year old girls will be defined as follows:

$$\frac{\overset{Number\;of\;fecund\;sexually\;active\;15-19\;year\;old\;girls\;reporting}{use\;of\;modern\;contraceptives\;at\;the\;time\;of\;the\;survey}}{Number\;of\;fecund\;sexually\;active\;15-19\;year\;old\;girls}$$

Modern contraception: male and female sterilisation, contraceptive implants, intrauterine contraceptive devices, injectables, contraceptive pill/oral contraceptives, emergency contraceptive pill, male condom, female condom, Standard Days Method, Lactational Amenorrhoea Method, diaphragm, spermicides, foams and jelly.

Sexually active girls: those who report having sexual intercourse in the last 12 months.

Fecund girls: those who have started menstruating, are not pregnant and do not report that they are infertile.

Secondary outcomes are outlined in table 3.

**Table 3 T3:** Primary and secondary outcomes

Outcome domain	Indicators
Primary outcome	Prevalence of modern contraceptive use among sexually active girls aged 15–19 years
Secondary outcomes	Age-specific fertility rates. Age at first birth. Unmet need for modern contraception among sexually active girls aged 15–19 years. Adolescent girls’ knowledge on the use of modern contraceptives to prevent unintended pregnancies. Adolescent girls’ agency (self-efficacy) to use modern contraceptives to prevent unintended pregnancies. Adolescent girls’ attitudes towards the use of modern contraceptives to prevent unintended pregnancies. Adolescent girls’ access to contraceptive services and products. Adolescent girls’ misconceptions about modern contraceptives. Community acceptance and social support for adolescent girls to adopt healthy sexual and reproductive health (SRH) behaviours, including use of modern contraceptives.

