## Introduction

In 2012, the global community launched the Family Planning 2020 (FP2020) initiative to reach 120 million new contraceptive users in developing countries by 2020.^1^ Specifically, it calls for meeting all women’s needs for modern contraception to prevent unintended pregnancies and reducing the high adolescent birth rates in the world’s poorest countries. Helping adolescent girls avoid unintended pregnancies can have far-reaching benefits for them, their children and societies as a whole.^2^ Complications of pregnancy and childbirth are the leading cause of death among girls aged 15–19 years,^3 4^ and babies born to adolescent mothers face greater health risks than those born to older women.^5^ Moreover, adolescent childbearing is associated with lower educational attainment, and it can perpetuate a cycle of poverty from one generation to the next.^3^

From 1990 to 2010, adolescent fertility rates declined in most countries.^6^ However, adolescent fertility rates remain high in many lower-income countries. In some countries, fertility rates are declining more slowly in adolescents than in older women.^1^ Nigeria, Ethiopia and Tanzania have among the highest rates of adolescent fertility globally, with 109, 57 and 118 births per 1000 girls aged 15–19 per year, respectively.^1^ Equally, these countries also have some of the lowest rates of use of modern contraception in adolescents. In Nigeria, 98.8% of married adolescent girls and 50.3% of unmarried sexually active adolescent girls do not use a modern contraceptive method.^7^ The equivalent figures are 68.2% and 42.5% in Ethiopia^8^ and 86.7% and 66.9% in Tanzania.^9^ Preventing pregnancy among adolescents is a global priority and new interventions are needed, particularly in countries like Nigeria, Ethiopia and Tanzania where adolescent fertility rates remain high.

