In Ethiopia and Tanzania, our hypothesis is that the prevalence of modern contraceptive use among sexually active girls aged 15–19 years living in areas where the A360 programme is implemented will increase between 2017 and 2019. The increase in mCPR will be greater than what would have been expected to have occurred in the absence of the intervention. The primary analysis will compare the proportion of sexually active girls who report using modern contraception at baseline and endline. Similar analyses will be performed to look at the intervention effect on secondary outcomes (table 3). We will use logistic regression models to adjust for potential confounders, including age, educational attainment, parity and marital status (Tanzania only). In addition, we will conduct the following secondary analyses:Dose–response: individual level of engagement with the A360 interventions will be measured at endline. We will use a series of questions to rank individuals by their level of engagement with the A360 interventions that are available in the place where they live. We will then use regression models to assess the strength of association between level of engagement with the A360 interventions and use of modern contraception. Our hypothesis will be that those who are more engaged will be more likely to use modern contraception. If the data are consistent with this hypothesis, this will provide additional evidence of the effectiveness of the intervention. Our analysis approach will try to capture exposure to the main components of the intervention and to capture overall exposure to the package of interventions. For example, if there are two main components of the intervention (A, B), then we may have three different exposure variables (A, B and a combination of A and B). There remains some uncertainty as to which intervention components will be implemented in each setting over the 2-year follow-up. A detailed analysis plan will be finalised prior to the endline data collection.Secular trends: mCPR data available from other sources for the time period 2015–2019 will be examined to assess whether changes in mCPR in A360 communities between 2017 and 2019 reflect background changes in mCPR or whether mCPR appears to have increased more than would be expected during this time period. Detailed contraceptive use data among adolescents do not exist for the specific geographical areas in our study. Potential sources of data include DHS (Tanzania, Ethiopia),^8 9^ PMA2020 (Ethiopia),^21^ and demographic surveillance site data from areas near to our study sites (Kisesa in Mwanza^22^; Kersa and Harar in Oromia^23^). These data are unlikely to be directly comparable but we believe that they will give a broad indication as to whether mCPR is increasing, static or decreasing in the regions our study are situated in. Specifically, we will undertake a ‘modified’ difference in difference analysis. Prior to analysis of the endline data, from available existing data we will estimate the absolute increase in mCPR rates that we would expect in the study communities if secular trends from other sources were replicated. In the ‘modified’ difference in difference analysis, we will subtract this expected change from the difference between endline and baseline mCPR rate. When presenting this ‘modified’ difference in difference analysis, we will also present our assessment of the likely comparability, accuracy and completeness of these alternative data sources.

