#### Nigeria

In Ogun State, among sexually active unmarried girls aged 15–19 years, we assumed that between 2017 and 2019, mCPR will increase from 64.4% to 65.6% in the absence of A360 and from 64.4% to 72.6% in the presence of A360. Based on these assumptions and those in tables 4 and 5, our target sample size is 12 020 unmarried girls aged 15–19 years.

**Table 4 T4:** Assumptions for key parameters required for sample size calculations

Parameter	Ogun* (%)	Nasarawa* (%)	Oromia† (%)	Mwanza‡ (%)
Proportion of 15–19-year-old girls who are married (or living together)	10	15	20	22
Proportion of 15–19-year-old girls who are unmarried (not currently married)	90	85	80	78
Proportion of unmarried 15–19-year-old girls who report sexual activity in the past year	15	15	–	25
Proportion of married 15–19 year olds who report sexual activity in the past year	97	97	97	97
Proportion of sexually active girls who are married	42	53	–	52
Proportion of sexually active girls who are unmarried	58	47	–	48
Proportion of households with resident who is female aged 15–19 years	19	29	27	34

Sources:

*Nigeria DHS 2013,^7^ Nigeria GHS 2016.^13^

†Ethiopia DHS 2011,^18^ Ethiopia Mini DHS 2014,^24^ Ethiopia census 2007.^14^

‡Tanzania DHS 2015–2016,^9^ Tanzania census 2012.^15^

DHS, Demographic and Health Survey.

**Table 5 T5:** Sample size estimates

Parameter	Ogun	Nasarawa	Oromia	Mwanza
Target sample of sexually active 15–19 year olds*	1413	3586	1132	1217
Total sample of all 15–19 year olds* Includes non-sexually active girls Taking into account 10% non-response	10 362	4067	1284	3314
Design effect	1.16	1.12	1.50	1.50
Sample size for survey†	12 020	4555	1926	4980

*Includes unmarried girls (Ogun); married girls (Nasarawa and Ethiopia); unmarried and married girls (Mwanza).

†Total sample of all 15–19 year olds × design effect.

In Nasarawa State, among sexually active married 15–19 year olds, we have assumed that between 2017 and 2019, mCPR will increase from 3.0% to 3.1% in the absence of A360 and from 3.0% to 5.1% in the presence of A360. Thus, 4555 married girls aged 15–19 years must be surveyed to achieve 90% power (table 5).

In addition, a sample of 250 cohabiting adults (Ogun) and 250 husbands/male partners (Nasarawa) will be interviewed.

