#### Ethiopia

In Oromia Region, among sexually active married girls aged 15–19 years, we have assumed that between 2017 and 2019, mCPR will increase from 44.0% to 50.8% in the presence of A360. Based on this assumption and those in table 4, 1926 married girls aged 15–19 must be surveyed to achieve 90% power (table 5). In addition, a sample of 128 husbands/male partners will be interviewed.

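### The primary outcome counts only fecund, non-pregnant girls, but the sample size and its 90% power are built on all sexually active girls, with no allowance for the exclusion

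*Protocol article*

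**What the plan says.** Under Study outcomes, the mCPR formula has fecund sexually active girls aged 15–19 in both numerator and denominator. Fecundity is defined there: "Fecund girls: those who have started menstruating, are not pregnant and do not report that they are infertile".

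The restriction is missing elsewhere. Table 3 lists the primary outcome as "Prevalence of modern contraceptive use among sexually active girls aged 15–19 years". For Ethiopia and Tanzania, the Data analysis section says: "The primary analysis will compare the proportion of sexually active girls who report using modern contraception at baseline and endline". The Nigerian hypothesis in that section likewise refers only to sexually active girls.

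In the Sample size section, the first row of Table 5 is "Target sample of sexually active 15–19 year olds": 1413 (Ogun), 3586 (Nasarawa), 1132 (Oromia) and 1217 (Mwanza). The next row adds girls who are not sexually active and is described as "Taking into account 10% non-response". A design effect follows. Table 4 has rows for marriage, sexual activity and household composition, and none for pregnancy or infecundity. The text states 90% power for Nasarawa, Oromia and Mwanza, and no power for Ogun. It describes the assumed mCPR values (3.0%, 44.0%, 26.7%) as applying among sexually active girls.

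**The concern.** A sample size should count the people who enter the primary comparison. Here the outcome definition removes pregnant girls, girls who have not started menstruating and girls who report infertility, after the target has been set on a wider group. If the target is exactly what 90% power needs, any exclusion uses up power that was not budgeted for.

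The denominator of the assumed rates matters just as much. A prevalence among all sexually active girls is lower than one among fecund girls if pregnant girls are not users. So either the count or the rates in the calculation are on a different denominator from the outcome. The looser wording in Table 3 and the Data analysis section also leaves room for results on the wider denominator. Pregnancy is a consequence of not using contraception, so that choice could move the estimate itself.

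**Working it through.** **1. Reproduce the plan's targets.** Alpha is not stated, so two-sided 5% is assumed. For two proportions with pooled variance, n per survey round = [1.96·√(2p̄(1−p̄)) + 1.2816·√(p₁(1−p₁)+p₂(1−p₂))]² / (p₂−p₁)².

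- Oromia, 44.0% to 50.8%: (1.96×0.7062 + 1.2816×0.7045)² / 0.068² = 1131.0, rounded up to 1132. Power at 1132 is 90.0%.
- Mwanza, 26.7% to 32.7%: (1.96×0.6462 + 1.2816×0.6448)² / 0.060² = 1216.7, rounded up to 1217. Power at 1217 is 90.0%.
- Nasarawa, difference in differences (3.0% to 3.1% against 3.0% to 5.1%): n = (1.96+1.2816)² × (2×0.03×0.97 + 0.031×0.969 + 0.051×0.949) / 0.020² = 3589 against the stated 3586, and power at 3586 is 90.0%. This reads 3586 as the size per arm and round. The article does not say so, but that reading reproduces the figure.

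These targets are the analysable numbers (before the design effect) that 90% power requires, with nothing to spare.

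**2. Look for a hidden fecundity allowance in Table 5.**

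- Ogun: 1413/0.15 × 1.1 = 10 362 (stated 10 362)
- Nasarawa: 3586/0.97 × 1.1 = 4067 (stated 4067)
- Oromia: 1132/0.97 × 1.1 = 1284 (stated 1284)
- Mwanza: sexually active share 0.22×0.97 + 0.78×0.25 = 0.408; 1217/0.408/0.9 = 3314 (stated 3314)

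Sexual activity and non-response account for every figure. No allowance is hidden.

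**3. Power when a fraction f is excluded.** The effective size becomes n(1−f). The article gives no value for f, so 10–25% is assumed. Three readings of the mCPR inputs are possible:

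- A: the stated rates are already on the fecund denominator and stay unchanged.
- B: the stated rates refer to all sexually active girls and excluded girls are non-users. The baseline is divided by (1−f) and the implied odds ratio is held: (0.508/0.492)/(0.440/0.560) = 1.31 in Oromia and (0.327/0.673)/(0.267/0.733) = 1.33 in Mwanza.
- C: as B, but both stated rates are divided by (1−f).

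| Site | f | n(1−f) | A | B: rates, power | C |
|---|---|---|---|---|---|
| Oromia | 10% | 1019 | 86.8% | 48.9% to 55.7%, 86.8% | 92.8% |
| Oromia | 25% | 849 | 80.2% | 58.7% to 65.1%, 77.9% | 97.3% |
| Mwanza | 10% | 1095 | 86.8% | 29.7% to 36.0%, 88.5% | 91.3% |
| Mwanza | 25% | 913 | 80.2% | 35.6% to 42.4%, 85.1% | 93.8% |

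Nasarawa, over 10% to 30% exclusion: A gives 86.7% falling to 77.4%; C gives 90.1% to 90.5%. Holding the odds ratio (B) gives 89.8% to 89.2%.

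**The case against.** The strongest objection is that the Sample size section describes the mCPR values as applying among sexually active girls. Taken literally, with pregnant girls as non-users, removing them raises both rates and their difference, and power does not fall (reading C). The arithmetic is right, and it is why no single power figure can be asserted. But it requires the absolute effect to grow in proportion to 1/(1−f). The Sample size section says the effect review worked in odds ratios. If the odds ratio is carried to fecund girls, the shortfall in Oromia and Mwanza remains. Further details are placed in supplementary file 1, which is not shown and may settle the denominator.

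It can also be said that Table 3 and the Data analysis section merely abbreviate one explicit formula. That is plausible, and it makes the wording fault small, but it does not supply the missing step in Table 5.

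Three stronger readings are tempting and are not supported.

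- **A fixed power of about 82%.** A reader might turn the Introduction's "109, 57 and 118 births per 1000 girls aged 15–19 per year" (Nigeria, Ethiopia, Tanzania) into pregnancy shares: 0.057×0.75/(0.20×0.97) = 22.0% in Oromia and 0.118×0.75/0.408 = 21.7% in Mwanza. This applies national rates to selected districts, counts nine months of recognised pregnancy per birth, and needs reading A. In Oromia it also assigns every birth to a married girl. The same married-only divisor in Nasarawa gives 0.109×0.75/(0.15×0.97) = 56%, which is implausible. Infecundity is not quantified at all.
- **Analysed counts below 1132 and 1217.** The surveys are inflated for the design effect. Oromia: 1926×0.9×0.97 = 1681 sexually active, or 1261 after 25% exclusion. Mwanza: 4980×0.9×0.408 = 1829, or 1372. Both exceed the targets. What falls is the effective size after dividing by 1.5: about 841 and 914.
- **Non-response mishandled in every setting.** Mwanza divides by 0.9. The other three multiply by 1.1, a difference of about 1%.

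**Conclusion.** The mismatch is certain: the outcome is defined on fecund, non-pregnant girls, the sample size on all sexually active girls, and Table 5 leaves no room between them. Its effect on power is conditional on two things the article does not give: the share excluded and the denominator of the mCPR inputs. For an assumed 10–25% exclusion, power in Oromia and Mwanza is about 87% to 80% with rates unchanged. With the odds ratio held it is 87–78% and 88–85% respectively (the Mwanza upper figure is 88.5% before rounding). Only scaling both rates keeps it above 90%. Nasarawa runs from about 87% to 77% for 10–30% exclusion with rates unchanged, but stays near 90% if both rates are rescaled. Ogun has the same missing step but no stated power to contradict. All figures assume two-sided 5% and normal approximations.

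**What to change.** 1. State which denominator the 44.0%, 26.7% and 3.0% inputs use, and the Ogun input likewise, citing supplementary file 1 if it is given there.
2. Add a row to Table 4 for the share of sexually active girls who are fecund and not pregnant, with its source, and carry it through Table 5 so that rates and counts are on the same denominator.
3. Keep the planned survey sizes and restate power as a range over plausible exclusions. The baseline survey can supply the observed share.
4. Use the Study outcomes denominator in Table 3 and throughout the Data analysis section.

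The cost is wording and a less favourable power statement in some settings. No extra recruitment is needed. It should be settled before the endline data are analysed.

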### Data analysis

In Nigeria, our hypothesis is that sexually active girls aged 15–19 years living in areas where the A360 programme is implemented will have a greater increase in use of modern contraception compared with sexually active girls aged 15–19 years living in areas where the A360 programme has not been implemented. We will estimate the intervention effect separately for Ogun and each LGA-pair in Nasarawa. The effect estimates will be obtained by subtracting the baseline mCPR prevalence estimates from the prevalence estimates at follow-up and then calculating the difference between the comparison and intervention LGAs (the difference in difference method). If the two effect estimates for Nasarawa are similar, then we will combine them (eg, by weighting by the inverse of the variance) to produce a single summary estimate for the state. Similar analyses will be performed to look at the intervention effect on secondary outcomes (table 3). The difference in differences analysis assumes a common trend in the outcome in both the intervention and comparison area. Even if the two areas differ in a number of characteristics, the analysis is valid provided the common trend assumption is upheld. We will measure potential confounders at baseline and endline and adjust our analysis for any compositional changes over time in these confounders.

In Ethiopia and Tanzania, our hypothesis is that the prevalence of modern contraceptive use among sexually active girls aged 15–19 years living in areas where the A360 programme is implemented will increase between 2017 and 2019. The increase in mCPR will be greater than what would have been expected to have occurred in the absence of the intervention. The primary analysis will compare the proportion of sexually active girls who report using modern contraception at baseline and endline. Similar analyses will be performed to look at the intervention effect on secondary outcomes (table 3). We will use logistic regression models to adjust for potential confounders, including age, educational attainment, parity and marital status (Tanzania only). In addition, we will conduct the following secondary analyses:Dose–response: individual level of engagement with the A360 interventions will be measured at endline. We will use a series of questions to rank individuals by their level of engagement with the A360 interventions that are available in the place where they live. We will then use regression models to assess the strength of association between level of engagement with the A360 interventions and use of modern contraception. Our hypothesis will be that those who are more engaged will be more likely to use modern contraception. If the data are consistent with this hypothesis, this will provide additional evidence of the effectiveness of the intervention. Our analysis approach will try to capture exposure to the main components of the intervention and to capture overall exposure to the package of interventions. For example, if there are two main components of the intervention (A, B), then we may have three different exposure variables (A, B and a combination of A and B). There remains some uncertainty as to which intervention components will be implemented in each setting over the 2-year follow-up. A detailed analysis plan will be finalised prior to the endline data collection.Secular trends: mCPR data available from other sources for the time period 2015–2019 will be examined to assess whether changes in mCPR in A360 communities between 2017 and 2019 reflect background changes in mCPR or whether mCPR appears to have increased more than would be expected during this time period. Detailed contraceptive use data among adolescents do not exist for the specific geographical areas in our study. Potential sources of data include DHS (Tanzania, Ethiopia),^8 9^ PMA2020 (Ethiopia),^21^ and demographic surveillance site data from areas near to our study sites (Kisesa in Mwanza^22^; Kersa and Harar in Oromia^23^). These data are unlikely to be directly comparable but we believe that they will give a broad indication as to whether mCPR is increasing, static or decreasing in the regions our study are situated in. Specifically, we will undertake a ‘modified’ difference in difference analysis. Prior to analysis of the endline data, from available existing data we will estimate the absolute increase in mCPR rates that we would expect in the study communities if secular trends from other sources were replicated. In the ‘modified’ difference in difference analysis, we will subtract this expected change from the difference between endline and baseline mCPR rate. When presenting this ‘modified’ difference in difference analysis, we will also present our assessment of the likely comparability, accuracy and completeness of these alternative data sources.

All analyses will be conducted in Stata V.15 and we will use weights and robust SEs to account for the cluster sampling design.

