#### Nigeria

The intervention will be evaluated in Ogun (South Nigeria) and Nasarawa (North Nigeria) through population-based surveys conducted at baseline (late 2017) and approximately 24 months after the start of the intervention. In Nasarawa, four LGAs consisting of two similar pairs have been selected for evaluation. Two of these will receive the intervention (one in each pair) and two will not, that is, they will act as comparisons. In Ogun, the evaluation will be conducted in only two LGAs (one intervention and one comparison).

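### Nasarawa gets one state-level answer only if its two pair estimates turn out similar, yet power is stated only for the state

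*Protocol article*

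**What the plan says.** The Nigeria design section describes the layout: "In Nasarawa, four LGAs consisting of two similar pairs have been selected for evaluation", with one intervention and one comparison LGA in each pair. The Data analysis section then states: "We will estimate the intervention effect separately for Ogun and each LGA-pair in Nasarawa". Each effect is obtained by subtracting baseline from follow-up mCPR and "calculating the difference between the comparison and intervention LGAs (the difference in difference method"). On a state result it says: "If the two effect estimates for Nasarawa are similar, then we will combine them (eg, by weighting by the inverse of the variance"). The weighting is offered as an example, and the section does not say what stands as the Nasarawa answer if the two are not combined.

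The sample size text for Nigeria plans Nasarawa as one unit. It assumes that "mCPR will increase from 3.0% to 3.1% in the absence of A360" and "from 3.0% to 5.1% in the presence of A360", and concludes: "Thus, 4555 married girls aged 15–19 years must be surveyed to achieve 90% power (table 5"). Table 5 has one Nasarawa column, with 3586 in the row "Target sample of sexually active 15–19 year olds". No power is given for a pair.

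**The concern.** The condition refers to the observed effect estimates, so the form of the Nasarawa result (one number or two) is fixed only once the effects are known. The only power statement belongs to the state. When the condition fails, that statement applies to nothing that is reported, and the reader is left with two estimates of much lower power and no rule for reading them together.

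Three things are at stake: the chance of obtaining a state result when the programme works, the false-positive chance if either pair may support a claim, and whether the state-level question has a defined answer at all.

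**Working it through.** **Inputs.** mCPR 3.0% to 5.1% with A360 and 3.0% to 3.1% without (Sample size, Nigeria), a difference in differences of 2.1 − 0.1 = 2.0 points. 3586 sexually active girls, design effect 1.12, 10% non-response (Table 5); 97% of married girls sexually active (Table 4). Two pairs of LGAs. Alpha and sidedness are not stated, so two-sided 5% is assumed. An equal split over LGAs and the same rates in both pairs are also assumed.

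**Reproducing the plan's figure.** The variance sum over the four cells is 0.0291 + 0.048399 + 0.0291 + 0.030039 = 0.136638. With (1.96 + 1.2816)² = 10.507, n per cell = 0.136638 × 10.507 / 0.020² = 3589, against 3586 stated. The inflation also reproduces: 3586 / 0.97 × 1.10 = 4067, and 4067 × 1.12 = 4555.

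**Two readings of 3586.** In that formula a cell is one arm in one survey. Elsewhere 4555 behaves as a state total per survey:
- Table 2 lists it for Nasarawa as a whole.
- The planned EAs yield about that many girls: 1150 × 100 × 0.29 × 0.15 × 0.9 ≈ 4502.
- One husband per 17 girls gives 4555 × 0.97 / 17 ≈ 260, against a target of 250.

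So both readings are carried: (A) 3586 is the state total per survey, or 3586 / 4 = 896.5 per LGA; (B) 3586 is per arm per survey, or 1793 per LGA.

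**Precision and power.** SE of a pair estimate = √(0.136638 / n per LGA). SE combined = SE pair / √2. SD of the difference between pairs = SE pair × √2. Power = Φ(2.0 / SE − 1.96).

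| | A | B |
|---|---|---|
| SE, one pair (points) | 1.23 | 0.87 |
| SE, combined | 0.87 | 0.62 |
| SD of difference between pairs | 1.75 | 1.23 |
| Power, one pair | 37% | 63% |
| Power, combined | 63% | 90% |
| Pairs differ by >1 point, equal true effects | 57% | 42% |
| Pairs differ by >2 points, equal true effects | 25% | 11% |

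**Chance of a significant state estimate under the rule.** With equal variances the combined estimate is independent of the difference between pairs, so this chance is power × probability of combining. Three meanings of similar are tried, all assumed: within 1 point, within 2 points, or a non-significant 5% heterogeneity test. With a true 2.0-point effect in both pairs:
- A: 63% × 43%, 75% or 95% gives 27%, 47% or 60%.
- B: 90% × 58%, 89% or 95% gives 52%, 81% or 85%.

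**False positives with no effect.** All cells are set at 3.0%. The combined estimate is tested at 5% if similar; otherwise each pair is tested at 5% and either may support a claim. Simulation (2 million draws, normal approximation) gives, in the same order, 11.4%, 10.9% and 8.0% under A, and 11.5%, 8.9% and 8.0% under B. A hand check of the last case: 95% × 5% + 5% × 65% = 8.0%, where 65% is the simulated chance that at least one pair is significant when the heterogeneity test is.

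**Coverage of the combined interval given that the pairs were combined.** In the same simulations it is 95.0% for every meaning tried, under both readings.

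**The case against.** The strongest case for the rule is that allocation within pairs was not random and validity depends on common trends. Discordant pairs may mean that this assumption failed in one of them, and declining to average them is then defensible. The pair estimates are also planned unconditionally; only the state summary is conditional. Both points are fair. They argue for showing the pairs and their heterogeneity, not for letting the observed agreement decide whether a state answer exists.

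A numerical criterion for similarity, and the final weights, may well sit in the country protocols or an analysis plan that is not shown. Their absence from an article is no fault. A threshold would still leave the decision to the results.

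Several stronger readings are tempting and are not supported:
- **That selection distorts the combined interval.** It does not; coverage stays at 95%. The inflated error comes from testing two pairs when they are not combined.
- **That chance mostly decides whether the pairs are combined.** This depends on a threshold the article does not give. Under a 5% heterogeneity test, pairs with identical effects would be combined 95% of the time.
- **That inverse-variance weights pull the state estimate towards the pair with lower mCPR.** This needs different baselines in the two pairs. The article plans with a single 3.0% and names those weights only as an example.
- **That combining restores 90% power.** It does so only if 3586 is per arm per survey. Which reading is right is a separate sample-size question.

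**Conclusion.** The concern holds in a limited form. The article states a results-dependent rule for the Nasarawa summary while power is stated for the state alone. Under either reading of 3586 a single pair falls well short of the planned 90% (37% or 63%), and the combined estimate does better (63% or 90%). The rule lowers the chance of a significant state estimate, by little under a heterogeneity test and by a lot under a 1-point limit. It also allows a false-positive chance of about 8–11% if uncombined pairs are each tested at 5%.

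The power figures rest on a two-sided 5% test, an equal split over LGAs and equal effects in both pairs. The figures on false positives and on the chance of a state result rest, in addition, on assumed meanings of similar. That the rule depends on the results, and that no result is named if the pairs differ, rests on the text alone.

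**What to change.** In the Data analysis section, replace the conditional sentence with a commitment: the primary Nasarawa result is one pair-stratified combined difference-in-differences estimate, reported whether or not the pairs look similar, with the weighting fixed before endline data are seen. Both pair estimates and a heterogeneity statistic are always shown beside it, as description and with no gate.

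This costs one sentence and no additional data. The downside is that an average is reported even when the pairs disagree, possibly because common trends failed in one of them. The side-by-side display makes that visible, and the text can say that a marked disagreement will be discussed in that light.
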